## Abstract

**Background:**

Knowledge of the prevalence of morbidity secondary to stroke is important for health care professionals, health care commissioners, third sector organizations, and stroke survivors to understand the likely progress of poststroke sequelae and to aid in commissioning decisions, planning care, and adjusting to life after stroke.

**Objective:**

The primary aim of the Morbidity PRevalence Estimate In StrokE (MORe PREcISE) study is to determine the prevalence of morbidity secondary to a stroke, predictors of morbidity, and trends in quality of life and functional status using patient-reported outcomes, cognitive and functional assessments.

**Methods:**

A total of 500 participants will be recruited across Wales and England within 14 days following an admission to a stroke unit for either an ischemic or hemorrhagic stroke as part of a multicenter cohort study. Participants are assessed at baseline ≤14 days poststroke and subsequently at 90 (± 14) days and 180 (± 14) days poststroke. At each time point, data will be collected relating to the following domains: participant demographics, routine clinical, patient reported, cognitive status, emotional well-being, and functional ability.

**Results:**

Recruitment commenced in October 2018 with 20 sites opened as of September 2019 and was closed on October 31, 2019.

**Conclusions:**

The primary outcome is the prevalence of morbidity at 6 months secondary to a stroke. Further analysis will consider temporal changes in the health-related domains to describe trends among baseline, 3-, and 6-month time points.

**Trial Registration:**

ClinicalTrials.gov NCT03605381; https://clinicaltrials.gov/ct2/show/NCT03605381

**International Registered Report Identifier (IRRID):**

DERR1-10.2196/15851

## Introduction

### Stroke Morbidity

There are 1.2 million stroke survivors currently living in the United Kingdom [1]. Although mortality as a consequence of stroke is decreasing [1,2], over two-thirds of stroke survivors have a form of disability on discharge from hospital [3]. During a stroke, hypoxic injury leads to neuronal death [4,5], which can occur in potentially any part of the brain. Thus, due to the diverse functions of the brain, stroke can lead to significant impairments to diverse functions and structures of the body, resulting in a significant prevalence of morbidity secondary to stroke [6].

The prevalence of morbidity secondary to stroke is of central importance to health professionals to understand the prognosis of the disease in patients under their care. Further, providing an accurate estimation of the prevalence of morbidity secondary to stroke will allow commissioners of care, planners, and third sector organizations to adapt to and answer the needs of a poststroke population. Additionally, information regarding the likely progression of impairments secondary to stroke is important to stroke survivors, allowing them to plan for the future and to adjust to life after stroke.

### Measures of Morbidity

Expanding data collection beyond current routinely collected data in stroke relates to the work undertaken by the International Consortium for Health Outcomes Measurement (ICHOM) [7] and their minimum outcome dataset for stroke [8]. In the ICHOM Standard Set for Stroke, a number of, what ICHOM terms, “variables” (demographic, clinical, and treatment) and “outcomes” (survival, disease control, and patient reported) are included. The ICHOM Standard Set for Stroke takes important steps to collect data outside of the process of care data in areas such as patient-reported outcome data, which includes domains such as toileting, walking, and assistance with feeding. However, the ICHOM group does not advocate the specific collection of data related to cognitive impairment or emotional problems secondary to stroke. This study will address this by the inclusion of measures of emotional problems and mild cognitive impairment. Therefore, the scope of this study is to build on routinely collected health care and poststroke data not currently collected by the ICHOM Standard Set for Stroke for the purpose of estimating morbidity prevalence.

### Aims and Objectives

This paper describes the protocol for the Morbidity Prevalence Estimate at 6 Months Following a Stroke (MORe PREcISE) study (ClinicalTrials.gov NCT03605381—Registered: 30/07/19). The primary objective is to determine the prevalence of morbidity at 6 months secondary to a stroke, predictors of morbidity, trends in health-related quality of life (HRQoL), and function. The definition of morbidity secondary to stroke includes the following: aphasia, anxiety, depression, dysarthria, dysphagia, hemianopia, hemiparesis, hemiplegia, hemi-inattention, cognitive impairment, and functional impairment including activities of daily living and social interaction or roles.

Therefore, this study will collect a wide range of data related to the most common morbidity secondary to stroke, from stroke onset to 6 months poststroke across England and Wales. The secondary objectives include describing trends in domains such as HRQoL from acute onset to 6 months poststroke. It will also explore trends in pre- and poststroke functional levels, as assessed by the Modified Rankin Scale (mRS) [9] from the prestroke period to 6 months poststroke. Lastly, trends in outcomes (patient reported, functional, treatment, and process of care) by geographical distribution, such as country, health board/trust, local authority, and hospital (research site) coverage, will be explored.

## Methods

### Study Design

This study uses a 6-month prospective cohort study of stroke survivors and aims to recruit 500 participants between August 2018 and October 2019. Data measuring morbidity will be collected at three distinct periods: baseline (≤14 days poststroke), 3 months, and 6 months poststroke. This takes place in 20 centers across England and Wales which routinely admit acute or hyperacute stroke patients (Textbox 1). All sites were selected after expressing an interest via the National Health Service (NHS) research networks, and the geographic spread was considered during site selection.

Participating research sites.Participants:
Aneurin Bevan University Health Board, South East Wales, United KingdomBronglais General Hospital, Aberystwyth, Wales, United KingdomGlangwili General Hospital, Carmarthen, Wales, United KingdomGloucestershire Royal Hospital, Gloucester, England, United KingdomKingston Hospital, London, England, United KingdomUniversity Hospital of Wales, Cardiff, Wales, United KingdomMorriston Hospital, Swansea, Wales, United KingdomNew Cross Hospital, Wolverhampton, England, United KingdomOxford University Hospitals, Oxford, England, United KingdomPeterborough City Hospital, Peterborough, England, United KingdomPrince Charles Hospital, Merthyr Tydfil, Wales, United KingdomPrincess of Wales Hospital, Bridgend, Wales, United KingdomSomerset Partnership (SOMPAR), Somerset, England, United KingdomSouthmead Hospital, Bristol, England, United KingdomUniversity Hospital Lewisham, London, England, United KingdomWest Middlesex University Hospital, London, England, United KingdomWithybush General Hospital, Haverfordwest, Wales, United KingdomWrexham Maelor Hospital, Wrexham, United KingdomYeovil District Hospital, Yeovil, England, United KingdomYsbyty Glan Clwyd, Bodelwyddan, Wales, United Kingdom

### Participants and Eligibility Criteria

Participants eligible to be recruited for this study include those aged 18 years or over with a clinical diagnosis of stroke, within the previous 14 days; cerebral infarct (ICD I63) [10]; intracerebral hemorrhage (ICD I61) [10]; or stroke not specified as hemorrhagic or infarction (ICD I64) [10]. Exclusion criteria include a diagnosis of transient ischemic attack (ICD G45) [10], subarachnoid hemorrhage (ICD I60) [10], or any condition defined under ICD G93 (eg, anoxic brain damage) [10]. Patients receiving palliative care or are eligible for palliative care are also excluded from this study.

#### Sample Size

In order to estimate the prevalence of stroke morbidity at 6 months, assuming a 35% morbidity rate, with a 95% CI width of ±5%, will require 350 stroke survivors. Assuming that there is a 30% dropout [11] at the 6-month visit, the aim is to recruit a minimum of 500 stroke survivors. This will be achieved by aiming to approach all appropriate inpatients fulfilling the eligibility criteria across the 20 sites. Stata Statistical software will be used for the analyses.

### Outcomes

The primary outcome is to quantify the prevalence of poststroke morbidity, at three time points, using a range of assessments and outcome measures, which are as follows:

Patient-reported outcomes:Patient-Reported Outcomes Measurement Information System Global Health Short Form-10 (PROMIS-10) [12].Three Questions from the Riksstroke [13].Two Questions from the ICHOM Standard Stroke Set for Stroke [8].Cognitive status:Short-Form Montreal Cognitive Assessment (SF-MoCA) [14] (domains, clock drawing, abstraction, five-word recall).Telephone Montreal Cognitive Assessment Short (T-MoCA-Short) [15] (domains, verbal fluency, orientation, five-word recall).Emotional well-being:Patient Health Questionnaire-4 (PHQ-4) [16].PHQ-9 [17].Generalized Anxiety Disorder-7 (GAD-7) [18].Functional ability:Modified Rankin Scale [9].Rankin Focused Assessment (RFA) [19].Treatment:Recurring stroke (cerebral infarct [ICD I63]), intracerebral hemorrhage [ICD I61], and stroke not specified as hemorrhage or infarction [ICD I64] [10].Process:Length of stay following primary admission for stroke.Readmission to hospital within 30 days of discharge.

### Data Collection

Following enrolment into the study, data collection is divided into three distinct periods: Period A (within 14 days from the onset of stroke), Period B (90 days poststroke ± 14 days), and Period C (180 days poststroke ± 14 days) as per the participant flow diagram (Figure 1). A standardized SPIRIT (Standard Protocol Items: Recommendations for Interventional Trials) [20] schedule of assessments is presented in Figure 2.

**Figure 1 figure1:**
[figure not shown]
Participant flow diagram. Electronic Case Report Form/Case Report Form (eCRF/CRF).

**Figure 2 figure2:**
[figure not shown]
SPIRIT (Standard Protocol Items: Recommendations for Interventional Trials) checklist. SF MoCA: Short-Form Montreal Cognitive Assessment; T-MoCA-Short: Telephone Montreal Cognitive Assessment Short; PROMIS-10: Patient-Reported Outcomes Measurement Information System Global Health Short Form-10; ICHOM: International Consortium Health Outcomes Measurement; PHQ-4: Patient Health Questionnaire-4; GAD-7: Generalized Anxiety Disorder-7; PHQ-9: Patient Health Questionnaire-9; mRS: Modified Rankin Scale; RFA: Rankin Focused Assessment.

#### Period A—Within 14 Days of Stroke Onset

Period A begins following consent or following consultee declaration with data collection attempted as soon as possible during the participant’s admission. Baseline data collection will occur at 14 days or less poststroke and before discharge from hospital. All data will be collected using Case Report Form A (CRF A). There is a further window of 24 hours available for data collection if necessary. Baseline data will not be recorded outside these time points. Additionally, provided consent was received before discharge, data collection from the participant may occur after discharge to the community if no opportunity arose prior to discharge.

The baseline data collected comprise participant demographic and routine clinical data including their prestroke lifestyle data, cognitive assessment, Patient Reported Outcome Measure (PROM), and anxiety and depression screen. Demographic data are collected via medical notes or a care team and then confirmed by the participant or participant’s family or friends. An equivalent process will be undertaken to gather prestroke lifestyle data.

During baseline data collection, a cognitive screen will be administrated in the form of a SF-MoCA [14]. Alongside this assessment, the participants are required to self-complete a PROM using the PROMIS-10 [12], Riksstroke questions [13], and ICHOM questions [8]. Participants will also self-complete a PHQ-4 [16]. If the PHQ-4 is positive, as indicated by a score ≥3 for the sum of questions 1 and 2 or 3 and 4, for anxiety or depression, the patient will then self-complete the PHQ-9 [17] and GAD-7 [18]. If the participants are unable to self-complete, the study allows for assessments or outcomes to be administered verbally.

To gain a representation of any prestroke disability in participants, a prestroke mRS [9] will be completed. This must be carried out by a suitably trained health care professional. RFA [19] will be carried out by a suitably trained health care professional for an estimate of the level of poststroke disability.

#### 60 Days Poststroke (± 7 Days)

Between Periods A and B at 60 days poststroke, it should be established whether the participant remains as an inpatient or is discharged. It should be ascertained whether the participant has deceased, had another stroke, or is eligible for or already receiving palliative care. In the case of further stroke or palliative status, a serious adverse event (SAE) form should be completed and the participant should be withdrawn from the study. In the event of an unscheduled admission, an adverse event or SAE form should be completed and the principal investigator (PI) should be informed. The PI makes the decision regarding whether the participant should continue to participate or be withdrawn from the study. Participants themselves or their consultees have the right to withdraw from the study at any time, without providing a reason.

The research site team will ensure the accuracy of participant’s address and contact details on file, which may be confirmed using primary and secondary care–linked health records to ensure accuracy. To ensure participant retention, following these checks, a study involvement reminder letter should be sent to the participant’s home address, provided they have been discharged.

#### Period B—90 Days Poststroke (± 14 Days)

At this point, within the study, it is expected that a large proportion of participants will reside in the community. Therefore, participants are to receive study follow-up via either telephone or face-to-face appointment [21]. Telephone appointments should be scheduled with the participant to complete the patient-reported aspect of CRF B via the telephone. Follow-up appointments should be arranged to fall within the 90 days (± 14 days) poststoke window of opportunity, and a maximum of three attempts should be made to contact the participant. In circumstances where three unsuccessful attempts have been made to contact the participant or if the window of opportunity has elapsed, then the participant is to be considered lost to follow-up.

Face-to-face appointments can be used by research sites as a first preference. Participants with either or both communication difficulties and prestroke or poststroke cognitive impairment should be offered the option of either face-to-face or telephone appointments. The face-to-face follow-up appointments should be conducted in accordance with procedures outlined in Period A (≤14 days poststroke) data collection.

If participants are yet to be discharged from the hospital by 90 days (± 14 days) poststroke or have been rehospitalized, for reasons other than further stroke, then participants can also be followed up with CRF B but in line with procedures outlined in Period A (≤14 days poststroke) data collection.

#### 150 Days Poststroke (± 7 Days)

This occurs between Periods B and C at 150 days poststroke (± 7 days). The procedure is identical to that outlined in the 60-day poststroke section of this protocol paper, which should be repeated at the 150-day poststroke (± 7 days) time point.

#### Period C—180 Days Poststroke (± 14 Days)

Data collection at this point is identical to Period B (90 days poststroke). The procedure for this period should be repeated exactly as outlined in the Period B section of this protocol paper using CRF C at the 180-day poststroke (± 14 days) window of opportunity.

#### Long-Term Data Collection

Further funding may be sought to obtain repeat data measurement at future time points, in keeping with the recommendation of the ICHOM Standard Set for Stroke. Currently, there are no defined plans for these types of data collection, but all data will be collected using assessments and outcome measures as outlined in the protocol presented in Figure 2.

### Completion of Assessments, Screens, and Patient-Reported Outcomes

Response options for these data are either complete or incomplete and whether the participant is able or unable to self-complete the relevant PROMs, cognitive screen, and anxiety and depression screen. If the participant is unable to self-complete, then the reason for non–self-completion is to be recorded. Where participants cannot self-complete but are able to give verbal responses, then baseline data collection of PROMs, assessments, and screens are to be administered verbally to ensure that all questions are completed. If the participant is unable to give responses when verbal administration is attempted, the reason for this noncompletion should be recorded on the CRF. Reasons for both non–self-completion and noncompletion of verbal administration should be identified as either potentially cognitive or physical impairment.

#### Cognitive Causes of Noncompletion

Cognitive causes of noncompletion should be recorded on the CRF, and no further attempt at patient-reported data collection should be made at this time. Cognitive causes of noncompletion include, but are not limited to, the following: confusion,drowsiness, history of dementia, aphasia—expressive or receptive, and anosognosia.

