#### Physical or Visual Causes of Noncompletion

If the suspected reason for non–self-completion is physical or visual impairment, then the participant is to be provided assistance to complete the PROMs, cognitive screen, and anxiety and depression screen. The administrator should read the question and note down the response. However, there should be no deviation from the wording of the questions or response options. Potential physical or visual deficits that could be expected are as follows: hemiparesis, hemiplegia, hemi-inattention, and hemianopia.

During Periods B and C, if the participant is unable to complete the PROM, cognitive screen, or anxiety and depression screening questions via telephone, a decision about whether a suitable alternative follow-up method is appropriate should be made. This is to be based on clinical judgment, provided the participant still wishes to continue in the study.

During collection of data, the use of secondary sources to aid data collection is permitted for the following; demographic, clinical, lifestyle, poststroke sequelae and functional assessments. The participant’s family, friends, care team, or medical notes are permissible sources of consultation. However, secondary sources are not permitted to aid the completion of the patient-reported data such as cognitive screen, PROM, or anxiety and depression screen.

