#### Missing Outcome Data

Due to the nature of our data collection methods, and evidence from previous studies of this nature, we anticipate negligible missing instrument levels, and in this case, a complete case analysis will be carried out. If the level of missing outcome data is not considered negligible (>5%), missing data will be explored for patterns of missingness and may be imputed using appropriate methods. Imputation methods will depend on the proportion of missingness and reason for the missing data.

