### Consent

#### Informed Consent

All potentially eligible participants will have the capacity to offer valid and informed consent assessed. Potentially eligible participants who do not have the capacity to offer informed consent can also take part in the study through the use of a consultee, thereby ensuring that the study cohort is representative of the poststroke population.

In line with the Mental Capacity Act (2005) England and Wales [23], the potentially eligible participant’s capacity to consent will be presumed unless it is established otherwise. Informed consent will be sought from those potentially eligible participants, where a lack of capacity to consent could not be established as outlined under the Mental Capacity Act (2005) [23].

All potentially eligible participants with the capacity to consent are to be presented with the most current version of the participant information sheet and given a minimum of 24 hours to consider their participation in the study and ask questions or request clarifications. Following this period, written informed consent will be sought from all potential participants with the capacity to consent from the PI or a registered health care professional delegated by the PI.

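### The 5% complete-case rule ignores that cognitive non-completion depends on the outcome, so 6-month cognitive impairment is likely to be understated

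*Protocol article*

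**What the plan says.** All references are to the protocol article.

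- **Aims and Objectives** defines the morbidity to be counted as "aphasia, anxiety, depression, dysarthria, dysphagia, hemianopia, hemiparesis, hemiplegia, hemi-inattention, cognitive impairment, and functional impairment", among other functional items. Cognitive impairment, anxiety and depression are therefore targets of the prevalence estimate. Under Outcomes, the cognitive and emotional measures are the SF-MoCA/T-MoCA-Short, PHQ-4, PHQ-9 and GAD-7.
- **Cognitive Causes of Noncompletion** gives the stopping rule for testing: "Cognitive causes of noncompletion should be recorded on the CRF, and no further attempt at patient-reported data collection should be made at this time". The causes given, as examples, are "confusion,drowsiness, history of dementia, aphasia—expressive or receptive, and anosognosia".
- **Physical or Visual Causes of Noncompletion** draws a line between two kinds of data. On one side, "secondary sources are not permitted to aid the completion of the patient-reported data such as cognitive screen, PROM, or anxiety and depression screen". On the other, "the use of secondary sources to aid data collection is permitted for the following; demographic, clinical, lifestyle, poststroke sequelae and functional assessments".
- **Missing Outcome Data** expects negligible missingness on the instruments, in which case "a complete case analysis will be carried out". Above 5% missing, patterns are explored and imputation is optional, with the method to depend on the proportion and the reason.
- **Data Analysis** puts every recruited participant in the analysis population.
- **Informed Consent** admits people without capacity through a consultee, "thereby ensuring that the study cohort is representative of the poststroke population".

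**The concern.** Someone too confused, aphasic or unaware of deficit to be tested gets no cognitive or mood score, and nobody else may supply one. The article does not say what outcome category that person then has. The only stated rule is the one for missing data, and it decides what is negligible by the proportion missing. Here the mechanism matters more: the score is missing because of a condition closely related to the one being counted. A small proportion missing for that reason can do more harm than a larger proportion missing by accident.

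At stake is the prevalence of cognitive impairment at 6 months, which the Introduction says should inform clinicians, commissioners and survivors. Models predicting cognitive morbidity would be fitted without the same participants. The consultee route brings these people into the cohort, and the complete-case rule then leaves them out of the cognitive estimate.

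**Working it through.** **Inputs from the article.** Sample Size: 35% morbidity, 95% CI of ±5 points, 350 survivors, 30% dropout, 500 recruited. Missing Outcome Data: trigger at 5%.

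**Inputs not in the article, so assumed.** *m* is the share of participants followed at 6 months who cannot be tested for a cognitive cause. *f* is the share of those who truly are impaired. *q* is the prevalence among the tested, set at 35% for illustration; the article uses that figure for morbidity overall, not for the cognitive domain.

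**1. The plan's own figures.** n = 1.96² × 0.35 × 0.65 / 0.05² = 3.8416 × 0.2275 / 0.0025 = 349.6, rounded up to 350. Then 350 / 0.70 = 500. Both reproduce.

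**2. Shortfall of the tested-only estimate, at or below the trigger.** Prevalence among all followed = (1 − m)q + mf. The tested-only estimate is q, so it is low by m(f − q). With m = 5% and f = 1: 0.95 × 0.35 + 0.05 × 1 = 38.25%, a shortfall of 3.25 points. In points:

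| m | f = 0.35 | f = 0.5 | f = 0.7 | f = 1 |
|---|---|---|---|---|
| 2% | 0 | 0.3 | 0.7 | 1.3 |
| 5% | 0 | 0.75 | 1.75 | 3.25 |

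The estimate is low whenever f exceeds q, and unbiased only if the untestable are impaired exactly as often as the tested.

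**3. Check with the other anchor.** Fix the true prevalence in everyone at 35%. The tested-only estimate is then (0.35 − mf)/(1 − m). At m = 5%: f = 1 gives 0.30/0.95 = 31.6% (3.4 low); f = 0.7 gives 0.315/0.95 = 33.2% (1.8 low); f = 0.5 gives 0.325/0.95 = 34.2% (0.8 low). The choice of anchor hardly matters.

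**4. Against the planned precision.** 3.25 / 5 = 0.65, so at the article's own threshold the worst case uses about two thirds of the half-width. The loss of precision is trivial: 350 × 0.95 = 332.5, and 1.96 × √(0.2275 / 332.5) = ±5.1 points. The interval barely widens and gives no sign of the bias.

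**5. Mood screens.** The direction is less certain, so bounds are the honest summary. With m = 5% and 35% positive among the tested, prevalence lies between 0.95 × 0.35 = 33.25% (none of the untestable positive) and 38.25% (all positive).

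**The case against.** Much can be said for the plan, and several points stand.

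- **Aphasia and function.** A reader might infer that aphasia prevalence is biased as well, since aphasia stops the testing. The article does not support this. Poststroke sequelae and functional assessments may come from family, care team or notes, so aphasia, other sequelae and mRS/RFA can still be recorded.
- **Participants are not removed from the study.** All recruited are in the analysis population. The stop holds only for the occasion. Period B, which Period C repeats, offers face-to-face appointments to people with communication or cognitive difficulty, and another method may be chosen if the telephone fails. This reduces the untestable share but does not remove it: the alternative is discretionary, face-to-face visits follow the Period A procedures, and Period C is the last planned collection.
- **Complete case is conditional.** A reader might carry the formula on to 10% or 20% untestable and quote shortfalls of 6.5 or 13 points. Those shares lie above the trigger, where the article plans exploration and possibly imputation that takes account of the reason, and the figures also assume that every untestable person is impaired. They are not the effect of the stated rule. It is fair to say that imputation above 5% is optional and no method is named.
- **The reasons are kept.** They are recorded on the CRF, so the information is not thrown away. No stated rule uses it at or below 5%.
- **Not every cause is a poststroke morbidity.** Drowsiness may pass, and a history of dementia may predate the stroke.
- **Condensed article, SAP not shown.** Classification detail may well sit there. The point here concerns a rule the article does state, with its numerical threshold.

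**Conclusion.** The point holds for the outcomes that need the participant's own answers. There, missingness for a cognitive cause depends on the outcome, and a threshold on the proportion missing cannot make it ignorable. At 5% untestable, cognitive impairment is understated by about 3.3 points if all the untestable are impaired, 1.8 if 70% are, and 0.8 if half are. These sizes rest on an untestable share and an impaired fraction that the article does not give, and on borrowing the overall 35% for the cognitive domain. The downward direction needs only that untestable participants are impaired more often than tested ones.

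For mood and quality of life, what can be said is that the data are not ignorably missing; the direction is not established. The article does not support a claim that aphasia or functional prevalence is biased, that these participants leave the study, or that a double-digit bias follows from the rule. It also needs to reconcile including all recruited participants in the analysis population with analysing complete cases.

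**What to change.** Change the analysis wording in Missing Outcome Data and Data Analysis:

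1. State that the 5% complete-case rule does not apply to non-completion with a recorded cognitive cause.
2. For cognitive impairment at 6 months, keep these participants in the denominator. Count confusion, aphasia or anosognosia that prevents testing as impaired, or report it as a separate category (not assessable, cognitive cause). Choose between the two before analysis.
3. Report drowsiness and history of dementia separately, since they may be transient or predate the stroke.
4. Give tested-only prevalence as the sensitivity analysis.
5. For PHQ-4/PHQ-9/GAD-7 and PROMIS-10, add a not-assessable row with best- and worst-case bounds.
6. Say how the all-recruited analysis population and the complete-case rule fit together, outcome by outcome.

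The cost is analysis work only: the reasons are already on the CRF, and no further data collection or contact with participants is needed. The downside is some misclassification. For instance, a person with aphasia who cannot take the test may have little other cognitive impairment. The tested-only analysis shows how much that matters.
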